## Methods/design

### Participants

Participants will be recruited using a comprehensive online and in-print advertisement strategy targeting Manitoba residents (e.g., local newspaper ads, social media ads on Facebook, and website ads on Yahoo and Google AdWords restricted to Manitoba residents). Advertisements will target gamblers who self-identify as being concerned about their gambling and are interested in participating in a study that aims to “find ways to help people who are worried about their gambling.” Prospective participants, 18 years or older who report gambling in the past 30 days, will be directed to complete a brief web-based screener that assesses problem gambling severity. The eligibility of individuals will be determined by their willingness to be followed up, and a current score of 3 or more on the Problem Gambling Severity Index (PGSI) [21]. Prior treatment access will be measured; however, it will not be used to determine eligibility as the intent of this trial is to evaluate the impact of the interventions within a real-world community setting. Similarly, co-occurring depression, anxiety, and illicit drug consumption will be measured but will not be used as exclusion criteria. Finally, while recruitment is not specifically targeted to attract problem drinking, it is anticipated that the trial will contain participants with and without co-occurring problem drinking. Based on the frequency of co-occurring problem drinking and gambling in the general population, it is estimated that approximately 50% of the sample will have co-occurring problem drinking [14, 22]. Participants in the first trial (examining the impact of combining an Internet intervention for gambling with one for mood and anxiety) will not be eligible to participate in the current trial.

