#### Baseline survey

The baseline survey will assess demographic characteristics (e.g., age, sex, education, marital status, income, and employment status), clinical characteristics (such as gambling frequency and severity, prior treatment use, problem drinking, illicit drug use in the past year, mental health issues, i.e., depressive/anxiety symptoms and general psychological distress), and quality of life (i.e., using the World Health Organization Quality of Life 8-item survey [29]).

The severity of problem gambling will be measured using the past year PGSI and the past 3-month version of the NORC DSM-IV Screen for Gambling Problems (NODS), which indicates DSM-IV defined severity [30, 31]. The NODS has been previously employed within a 1-year follow-up study to assess brief treatment and its utility as an outcome measure [32]. Additionally, the mean number of days gambled in the past 3 months, the amount spent on gambling, and forms of gambled engaged in will be assessed. The use of treatment services for gambling concerns will be measured by asking participants to identify services accessed from a comprehensive list of treatment forms, as used in previous studies [4, 6]. Lastly, participants will also be asked to identify a treatment goal (quit or reduced gambling) and their perceived success in achieving that goal over the following 3 and 6 months on a Likert scale ranging from 0 “not at all” to 10 “extremely.” The primary outcome variables for gambling will be the NODS and number of days gambled.

Hazardous alcohol consumption will be measured using a past 3-month version of the Alcohol Use Disorders Identification Test, with the frequency of heavy drinking occasions modified for female and male participants (i.e., five or more drinks for males and four or more drinks for females) [33]. A score of 8 or more will indicate problem drinking. The primary outcome variable for alcohol consumption will be number of drinks consumed in a typical week.

The severity of depressive and anxiety symptoms will be measured using the Patient Health Questionnaire 9-item scale (PHQ-9) [34] and the Generalized Anxiety Disorder 7-item scale (GAD-7) [35], respectively. In addition, general psychological distress will be measured using the Kessler 10 questionnaire (K10), as this measure has been found to be responsive to change over time. The K10 has been well validated and is appropriate for self-administration, as it is brief, simple, and easy to comprehend [36, 37].

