## Discussion

Many problem gamblers are also problem drinkers [13, 14, 17–20], with a lifetime prevalence as measured by nationally representative samples ranging from 45% to 73% [14, 22]. Heavy drinking often occurs while problem gamblers are engaging in gambling activities [42], resulting in increased risky gambling behavior [43–45]. Further, co-occurring problem drinking negatively impacts the treatment outcomes of problem gamblers (see the systematic review by Merkouris et al. [46]). Targeting problem drinking by problem gamblers may have the dual benefits of reducing both the problem drinking itself and of acting as a mediator for reductions in problem gambling behavior.

The proposed study seeks to determine whether providing simultaneous Internet interventions for gambling and drinking is of benefit for those with these co-occurring problems. More specifically, it will evaluate whether there is an incremental benefit to providing access to a problem drinking Internet intervention (G + A intervention) in addition to an Internet intervention for problem gambling (G-only intervention) for individuals with gambling problems who do or do not have co-occurring problem drinking. A limitation of the current trial is its short follow-up period (6-month follow-up). If the trial finds that the addition of a brief alcohol intervention to an online gambling intervention is beneficial at this time point, then future research examining any sustained impact of the intervention would be merited. The results of this study will enhance our understanding of Internet interventions for addictions in general, as well as inform how treatments can be developed and matched to the care of and needs for those with co-occurring problem gambling and drinking.

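### The 50% problem-drinker share rests on references described as giving lifetime prevalence, but the trial counts past-3-month AUDIT scores of 8 or more, so the key subgroup's size has no matching basis

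*Protocol article*

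**What the plan says.** Three places in the protocol article bear on this.

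- **Participants.** The estimate is introduced with "Based on the frequency of co-occurring problem drinking and gambling in the general population", and then "it is estimated that approximately 50% of the sample will have co-occurring problem drinking", citing references 14 and 22. No time window is given. The section adds that recruitment is not aimed at problem drinkers, and it sets no drinking entry criterion or quota.
- **Discussion.** The co-occurrence of problem drinking is described as a "lifetime prevalence as measured by nationally representative samples ranging from 45% to 73" per cent, citing the same references 14 and 22.
- **Baseline survey.** Drinking is classified with a "past 3-month version of the Alcohol Use Disorders Identification Test", and "A score of 8 or more will indicate problem drinking".

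Under Major research questions, the predicted benefits in Hypotheses 1 and 2 are for problem drinkers, and Hypothesis 3 concerns only problem drinkers in the G + A arm. The Power analysis says that 280 recruited and 224 followed up suffice to test the hypotheses, with power 0.80 at alpha 0.05 for a difference of two gambling days per month or one NODS point. It does not mention the 50% share or a subgroup size.

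**The concern.** The only figure given for the size of the decisive subgroup cites sources that the article elsewhere describes in lifetime terms, while membership will be decided by the past 3 months. For one condition in one population, a 3-month prevalence cannot exceed the lifetime prevalence, because people who have remitted count only in the latter. A reader of the Participants section cannot see the mismatch, since no time window is named there.

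The precision of the Hypothesis 1 contrast depends directly on how many problem drinkers enter. If the share falls below 50%, nothing described in the article would correct it. The subgroup comparison would then be less informative than a reader would expect from the claim of sufficient power.

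**Working it through.** **1. The passages side by side.**

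| | Participants (the 50%) | Discussion (45% to 73%) | Baseline survey (trial definition) |
|---|---|---|---|
| Source | refs 14, 22 | refs 14, 22 | AUDIT |
| Time window | not stated | lifetime | past 3 months |
| Population | general population | nationally representative samples | self-referred gamblers with PGSI of 3 or more |
| Condition | problem drinking | problem drinking, measure not described | AUDIT score of 8 or more |

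The time window described for the sources differs from the trial's. The population differs, and the condition may differ.

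**2. The plan's own figure.** 280 × (1 − 0.20) = 224, so the attrition step reproduces. The 0.80 cannot be reproduced because the article gives no standard deviation. The calculation below therefore takes the 0.80 as given and rescales it, which makes the unknown standard deviation drop out.

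**3. Inputs.** 224 followed up, power 0.80, alpha 0.05, and 2 days or 1 NODS point (Power analysis). My assumptions are a two-sided test, 1:1 allocation, a two-sample comparison of completers, equal attrition, and the same standard deviation in the subgroup as overall. The documents give no past-3-month share, so 20% to 50% is an assumed range.

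**4. Reading A: the 0.80 applies to all 224 (112 per arm).** A two-sample t-test with 222 degrees of freedom has power 0.80 at noncentrality 2.814. For a share p:

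- per arm = 112p
- noncentrality = 2.814 × √p, with 224p − 2 degrees of freedom
- detectable difference ≈ 2/√p days or 1/√p NODS points

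| Share p | Randomised (280p) | Followed up (224p) | Per arm | Noncentrality | Power | Detectable days | Detectable NODS |
|---|---|---|---|---|---|---|---|
| 50% | 140 | 112 | 56 | 1.990 | 0.50 | 2.8 | 1.4 |
| 40% | 112 | 90 | 45 | 1.780 | 0.42 | 3.2 | 1.6 |
| 30% | 84 | 67 | 34 | 1.541 | 0.33 | 3.7 | 1.8 |
| 20% | 56 | 45 | 22 | 1.258 | 0.23 | 4.5 | 2.2 |

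A normal approximation gives values no more than 0.01 higher.

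**5. Splitting the loss.** The fall from 0.80 to about 0.50 occurs at the article's own 50% share. It comes from applying whole-sample power to a subgroup. The share accounts only for the steps below that, for example 0.50 to 0.42 at a 40% share or 0.50 to 0.33 at 30%.

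**6. Reading B: the 0.80 was meant for a 50% subgroup (56 per arm).** With 110 degrees of freedom the noncentrality is 2.826, and for a share p it is 2.826 × √(p/0.5). Power is 0.80 at 50%, 0.71 at 40%, 0.58 at 30% and 0.42 at 20%. Here the whole loss is due to the share.

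**7. Scope.** These figures concern Hypothesis 1 only. The article states no drinking difference for Hypothesis 2, and Hypothesis 3 compares participants within one arm, so the power values do not carry over to them.

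**The case against.** The strongest replies are these.

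- **The 50% may not be the lifetime figure.** The Participants section gives no window, and two references can report both lifetime and current figures. This stands as a limit: that the 50% was lifted from lifetime prevalence is an inference from the shared citations. What the article shows is that the only description it gives of those sources' figures is a lifetime one.
- **The direction is not shown.** A reader might infer that the subgroup must come out smaller than estimated. The inequality between current and lifetime prevalence needs the same condition and the same population. An AUDIT score of 8 or more is introduced as a measure of hazardous consumption and may be broader than the measure in the cited surveys. The sample is self-selected gamblers, and 50% already lies near the low end of 45% to 73%. This stands: a lower share is plausible, not established.
- **No calculation uses the 50%.** This is correct. A reader might infer an arithmetic error in the sample size, but correcting the share would change no figure in the Power analysis. The point is that the section claims sufficient power for hypotheses resting on a subgroup whose size it never states.
- **The power figures borrow from a different weakness.** In part they do. A reader might blame the whole fall from 0.80 on the prevalence mismatch, but the first step, to about 0.50, comes from testing a subgroup.
- **The planned models use more data than completers.** The Data analysis section specifies mixed models on all available data, so the figures are approximate. The dependence of precision on the share remains.

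**Conclusion.** The mismatch holds and can be verified within the article. The 50% share cites sources described in lifetime terms, whereas the trial counts a past-3-month AUDIT score of 8 or more. The share used for planning therefore lacks a basis in the quantity that will be observed. Neither the size nor the sign of any error can be derived from the documents.

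The consequence is conditional. Over the assumed range of 50% down to 20%, Hypothesis 1 power for the stated differences runs from about 0.50 to 0.23 if the 0.80 refers to all 224, or from 0.80 to 0.42 if it was meant for a 50% subgroup. Both rest on two-sided testing, 1:1 allocation and equal variance in the subgroup. The documents do not support the stronger conclusion that the trial will fall short of a planned subgroup size: no such size is planned, and no current prevalence is given. This is a planning assumption and a power statement that should be corrected, not an error that invalidates the design.

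**What to change.** - **Participants:** state the share as an assumption for a past-3-month AUDIT score of 8 or more, with its justification, and say there that the prevalence cited is lifetime.
- **Power analysis:** say whether the 0.80 refers to the whole sample or to problem drinkers. Give the subgroup size and the Hypothesis 1 power or detectable difference over an assumed range such as 20% to 50%.
- **During the trial:** count the pooled share with an AUDIT score of 8 or more from baseline data, without reference to arm, and restate the precision of the subgroup comparisons before unblinding.

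Recruitment should stay as it is. Moving advertising towards drinkers would change the population the trial sets out to study and could signal an alcohol focus in a trial described as double-blinded.

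The cost is a few sentences, a small table and a count from data already collected at baseline. Randomisation and eligibility do not change. The downside is that the planning figures will look less favourable.

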### Study design and procedures

The proposed study is a two-arm double-blinded parallel-group RCT comparing two online interventions over a 6-month period: an intervention targeting gambling issues only versus one that contains interventions for hazardous alcohol consumption. Potential participants, who respond to the advertisement by clicking on the link or visiting the website, will be provided first with a brief description of the study prior to completing an eligibility screener. Individuals who are found to be eligible will be asked to provide contact information in the form of an email address. Subsequently, potential participants will be sent an email with a link to an online consent form. Participants will be asked to provide their telephone number and mailing address as additional contact information, as well as to provide permission for study staff to contact them via phone or mail for follow-up surveys if correspondence by email is unsuccessful. Those who complete the consent form and provide a real postal address will be sent a link to complete the baseline questionnaire and will be randomized into one of the two experimental conditions. Randomization will be stratified on age, sex, and prior use of treatment using an automatized algorithm to ensure a random distribution of prognostic indicators at baseline. To reduce attrition in the study, those who complete the baseline questionnaire and access the online intervention will receive a $10 Amazon.ca gift certificate. At 3 and 6 months post-randomization, all participants will receive an email request to complete a follow-up survey in the form of a hyper-linked web address. In addition, up to two email reminders for follow-up survey completion will be sent to participants to promote retention in the study. Furthermore, participants who complete the 3-month follow-up will be sent a $20 gift certificate and those who complete the 6-month follow-up will be sent an additional $30 gift (i.e., a total honorarium of $60 for each participant including the amount given at the baseline). Lastly, participants in both the G-only and the G + A interventions will receive an additional three emails encouraging the use of each respective intervention. See Fig. 1 for a Consort diagram summarizing the study design.

**Fig. 1 Fig1:**
[figure not shown]
Overview of the proposed intervention trial. fu follow-up, PGSI Problem Gambling Severity Index

### Ethical approval

This study, including methods and design, has been approved by the standing ethics review committee of the Centre for Addiction and Mental Health (CAMH).

### Interventions

#### G-only

The gambling only Internet intervention will consist of self-change tools developed by Hodgins et al. [23] that have been adapted to an online interface. Three separate trials have demonstrated the significant impact of these tools on gambling [4, 6, 7], and their successful use within an online format has also been previously documented [8, 9]. The intent of these tools is to provide individuals with both behavioral and cognitive strategies that assist in the recovery from or a reduction in gambling.

#### G + A

The gambling plus alcohol intervention will consist of the G-only intervention as well as access to a study specific version of Check Your Drinking (CYD). The CYD contains a brief 18-item screener that has been designed to assess the quantity and frequency of drinking, and the severity of hazardous drinking [24]. Following the completion of the 18-item screener, the user is provided with a personalized report that contains normative feedback (i.e., it compares the person’s drinking with the drinking of others in the general population of the same age, sex, and country of origin, such as Canada, the U.S.A., and the U.K.). The CYD has been subjected to five randomized controlled trials from two independent research groups, all of which displayed its significant impact by reducing hazardous alcohol consumption compared to controls [24–28].

Both versions of the website contain a link to a page listing resources to contact in case of a crisis.

### Measures

Assessment points and instruments are presented in Fig. 2, and the SPIRIT checklist is available as Additional File 1.

**Fig. 2 Fig2:**
[figure not shown]
Study assessment points and instruments

#### Baseline survey

The baseline survey will assess demographic characteristics (e.g., age, sex, education, marital status, income, and employment status), clinical characteristics (such as gambling frequency and severity, prior treatment use, problem drinking, illicit drug use in the past year, mental health issues, i.e., depressive/anxiety symptoms and general psychological distress), and quality of life (i.e., using the World Health Organization Quality of Life 8-item survey [29]).

The severity of problem gambling will be measured using the past year PGSI and the past 3-month version of the NORC DSM-IV Screen for Gambling Problems (NODS), which indicates DSM-IV defined severity [30, 31]. The NODS has been previously employed within a 1-year follow-up study to assess brief treatment and its utility as an outcome measure [32]. Additionally, the mean number of days gambled in the past 3 months, the amount spent on gambling, and forms of gambled engaged in will be assessed. The use of treatment services for gambling concerns will be measured by asking participants to identify services accessed from a comprehensive list of treatment forms, as used in previous studies [4, 6]. Lastly, participants will also be asked to identify a treatment goal (quit or reduced gambling) and their perceived success in achieving that goal over the following 3 and 6 months on a Likert scale ranging from 0 “not at all” to 10 “extremely.” The primary outcome variables for gambling will be the NODS and number of days gambled.

Hazardous alcohol consumption will be measured using a past 3-month version of the Alcohol Use Disorders Identification Test, with the frequency of heavy drinking occasions modified for female and male participants (i.e., five or more drinks for males and four or more drinks for females) [33]. A score of 8 or more will indicate problem drinking. The primary outcome variable for alcohol consumption will be number of drinks consumed in a typical week.

The severity of depressive and anxiety symptoms will be measured using the Patient Health Questionnaire 9-item scale (PHQ-9) [34] and the Generalized Anxiety Disorder 7-item scale (GAD-7) [35], respectively. In addition, general psychological distress will be measured using the Kessler 10 questionnaire (K10), as this measure has been found to be responsive to change over time. The K10 has been well validated and is appropriate for self-administration, as it is brief, simple, and easy to comprehend [36, 37].

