**Methods:**

Potential participants will be recruited online via a comprehensive advertisement strategy, if they meet the criteria for problem gambling. As part of the baseline measures, problem drinking will also be assessed. Eligible participants (*N* = 280) who agree to partake in the study and to be followed up for 6 months will be randomized into one of two versions of an Internet intervention for gamblers: an intervention that targets only gambling issues (G-only) and one that combines a gambling intervention with an intervention for problem drinking (G + A). For problem gamblers who exhibit co-occurring problem drinking, it is predicted that participants who are provided access to the G + A intervention will demonstrate a significantly greater level of reduction in gambling outcomes at 6 months compared to those provided access to the G-only intervention.

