### Major research questions

The proposed trial will compare the efficacy of two Internet interventions: an intervention that just targets gambling issues (G-only) versus one that contains an intervention for problem drinking in addition to an intervention for gamblers (G + A). Outcome variables for gambling will measure the reduction in gambling severity and frequency of gambling. The outcome for a reduction in alcohol use will be measured by the reduction in the frequency of drinking during the past week. The primary hypotheses are:**Hypothesis 1:** For problem gamblers with co-occurring problem drinking, it is predicted that participants provided access to the G + A website will display significantly reduced gambling outcomes at the 3- and 6-month follow-ups compared to those provided access to the G-only website. For problem gamblers without co-occurring problem drinking, there will be no significant difference between those provided access to the G-only and G + A websites at the 3- and 6-month follow-ups.**Hypothesis 2:** For problem drinkers, it is predicted that participants provided access to the G + A website will display significantly reduced drinking outcomes at the 3- and 6-month follow-ups compared to those provided access to the G-only website. For participants who are not problem drinkers, there will be no significant difference in drinking between those provided access to the G-only and G + A websites at the 3- and 6-month follow-ups.**Hypothesis 3:** Problem gamblers with co-occurring problem drinking who receive the G + A intervention and reduce the amount they drink between the baseline and 3-month follow-ups will display significantly improved gambling outcomes at the 6-month follow-up compared to problem drinkers who receive the G + A intervention but experience no decrease in their drinking.

Follow-ups at 3 and 6 months were chosen as it is unknown whether the intervention will have the predicted impact, and we wished to optimize the possibility of finding an effect by employing a short-term follow-up.

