### Power analysis

Efforts will be made to recruit a total sample of 280 participants, and we anticipate that 224 participants will be successfully followed up at 6 months (i.e., estimated 20% attrition based on previous research of online interventions, albeit targeting hazardous alcohol use) [40]. This sample size will provide sufficient power to conduct the proposed statistical analyses necessary to test the aforementioned hypotheses. Based upon previous data collected by Hodgins et al. [4, 6] on gambling frequency and NODS scores, and assuming that a correlation of 0.5 exists between baseline and follow-up measures, then power = .0.80 and α = .05. This sample size is sufficient to detect a difference of at least two gambling days per month between both experimental conditions in both the 3- and 6-month follow-up periods. Smaller differences in gambling days per month may not be clinically meaningful. Similarly, the proposed sample size will also be sufficiently powered to detect a 1-point difference of NODS scores at the 6-month follow-up. Calculations are based upon a repeated measures ANOVA model (G.Power 3.1.9).

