### Data analysis

The two primary hypotheses of this study, which focus on comparing outcomes between groups for gambling and drinking respectively, will be analyzed using linear mixed-effect models with random intercepts. This will allow us to use all available participant data within the models, employing a restricted maximum likelihood to handle missing data. Separate analyses will be conducted for each primary outcome variable (i.e., NODS score, mean number of day gambled in the past month, and, for drinking, the number of drinks consumed in a typical week). For secondary analyses, mixed-effects models will be conducted to examine the effect of moderators on primary variables, that is, additional fixed-effect interactions will be included in exploratory models (e.g., extent of intervention use, participants’ sex, severity of gambling and drinking at baseline, and co-occurrence of mental health concerns). In addition, secondary analyses will also examine predictors of treatment use, as well as the effect of accessing treatment on primary outcomes. The third hypothesis, comparing the potential moderating effect of reductions in drinking on gambling severity, will be examined using Hayes’s Process macro. This method uses a state-of-the-art regression-based conditional process approach [41] to estimate covariances, variances, and means. Missing data will be handled using a maximum likelihood approach. Finally, we will examine whether changes in quality of life are related to improvements in gambling outcomes.

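### Two unranked primary gambling outcomes, with the primary visit and the rule for claiming Hypothesis 1 not fixed, so the stated alpha of .05 and power of 0.80 do not describe that claim

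*Protocol article*

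**What the plan says.** All references are to the protocol article.

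- **Outcomes.** Under Baseline survey: "The primary outcome variables for gambling will be the NODS and number of days gambled". Neither is ranked above the other.
- **Analysis.** Under Data analysis: "Separate analyses will be conducted for each primary outcome variable". The gambling and drinking hypotheses "will be analyzed using linear mixed-effect models with random intercepts". The section does not say whether the treatment contrast is taken at each visit or overall.
- **Visit.** The abstract predicts that problem drinkers given G + A "will demonstrate a significantly greater level of reduction in gambling outcomes at 6 months". H1, under Major research questions, says they "will display significantly reduced gambling outcomes at the 3- and 6-month follow-ups". The Power analysis section claims a detectable difference of two gambling days per month at both follow-ups, but one NODS point at 6 months only.
- **Error rate.** Power analysis gives "power = .0.80 and α = .05" (the power value has a stray point). It is not divided between outcomes or visits.

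No section says whether one, some or all of these results must be significant for H1 to be supported.

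**The concern.** H1 is the main claim of the trial. Two outcomes and two visits give up to four treatment comparisons behind it. If the rule for success is open, the outcome and visit that carry the claim can be chosen after the results are seen. A single alpha of .05 then need not be the error rate of the claim. If instead every result is required, 0.80 is not its power. A reader of the published result could not tell which standard it had met.

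The primary outcome, the time point and the hypothesis are matters that a protocol settles, and this one states them. The difficulty is that its statements on the visit differ and do not add up to one rule.

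**Working it through.** **Inputs from the document.** Alpha .05 (sidedness not stated; two-sided assumed); power 0.80; 280 randomized and 224 followed up at 6 months; correlation 0.5 between baseline and follow-up.

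**Inputs assumed.** The correlation between NODS and days gambled, and between the 3- and 6-month comparisons, is not given. Values from 0 to 0.7 were used for each.

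**The plan's own figures.** Attrition reproduces: 280 × (1 − 0.20) = 224. Power cannot be reproduced because no standard deviation is given. At 112 per arm the detectable standardized difference is (1.960 + 0.842) × √(2/112) = 0.374 for a follow-up score. Adjusted for baseline at r = 0.5 it is 0.374 × √0.75 = 0.324. The stated differences then imply SDs of 2/0.374 = 5.3 to 2/0.324 = 6.2 days, and 1/0.374 = 2.7 to 1/0.324 = 3.1 NODS points. Below, the 80% is taken at face value for each comparison.

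**False-positive rate for H1, by reading.** With k independent tests the rate is 1 − 0.95^k: 9.75% for k = 2 and 18.5% for k = 4. Correlated cases were simulated with multivariate normal test statistics, counting |z| > 1.96.

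| Reading of H1 | False-positive rate |
|---|---|
| Either outcome, at 6 months only or in one overall test per outcome | 9.75% (r = 0), 9.1% (0.5), 8.3% (0.7) |
| Either outcome at either visit | 18.5% (both r = 0), 16.2% (both 0.5), 13.7% (both 0.7) |
| Both visits, same direction, on either outcome | about 0.9% to 3.3% for visit correlations 0.3 to 0.7; about 0.25% at 0 |
| All four results | 0.08% (both 0.5), 0.4% (both 0.7) |

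These count results in either direction. Counting only results that favour G + A, the second row becomes about 7-10%, against a nominal 2.5%.

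**Power when both outcomes are required.** With 80% power for each outcome at one visit, joint power is 0.80² = 64% if they are independent, 69% at r = 0.5 and 71% at r = 0.7.

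**Cost of Holm across two outcomes.** The first step tests at 0.025. The detectable difference is multiplied by (2.241 + 0.842)/(1.960 + 0.842) = 1.10. At the original difference, power for one outcome at that step is Φ(2.802 − 2.241) = 71%. If both effects are present at the planned size, the chance that at least one outcome succeeds is 82% (r = 0.7) to 92% (r = 0).

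**The case against.** **The text does not set up four tests.** A reader might infer that H1 can be claimed on any of four tests, each at 0.05, with a false-positive rate of about 15%. The document does not say that. Alpha .05 appears only in the power section, and the mixed model may give a single test per outcome. H1 joins the visits with an and, which can be read as requiring both. This objection stands: 14-18.5% is the rate under the most liberal reading and not a property of the plan. Under the strictest readings the error rate is below 5%.

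**The visits are not in flat contradiction.** The abstract condenses H1, and 6 months is one of H1's two visits. The abstract and the NODS power statement both point to 6 months. This stands in part. It makes 6 months the natural choice, but no section designates it, and even at 6 months alone two tests leave about 8-10% if either suffices.

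**Multiplicity may be handled in an analysis plan that is not shown.** That is fair for the adjustment method, and its absence is not the finding. It does not dispose of the point. The outcomes and visits are set out here inconsistently, and the power is computed at an undivided .05, which a later adjustment would no longer match.

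**Pooling the drinking hypothesis.** A reader might add Hypothesis 2 and quote a larger error rate. It is numbered separately and has its own outcome, so it is not counted.

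**Conclusion.** The point holds as an unfixed primary visit and success rule for H1, not as a demonstrated 15% error rate. Depending on the reading, the false-positive rate runs from well under 5% (both visits or all results required), through about 8-10% (two tests), to about 14-18.5% (any of four). Where both outcomes must be significant, joint power is about 64-71%. Requiring both visits on either outcome is the one reading that keeps the error rate below 5% without requiring both outcomes, and the protocol does not adopt it.

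The figures assume two-sided 0.05 tests, approximately normal test statistics, the correlations stated above and the plan's 80% for each single comparison. The correlations change the size within each reading but not the ordering. The choice should be settled before outcome data are examined.

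**What to change.** Reconcile the abstract, H1 and the Power analysis section in one paragraph:

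1. Name 6 months as the primary visit for H1, as the abstract does, with 3 months secondary.
2. State the model contrast that tests H1 at that visit.
3. Test NODS and days gambled with Holm at an overall two-sided 0.05, and state that H1 is supported for whichever outcome passes.
4. Keep Hypothesis 2 (drinks in a typical week) as its own family.
5. Restate the power to match.

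The cost is the first-step detectable difference, about 10% larger: two gambling days becomes about 2.2 and one NODS point about 1.1. Equivalently, each outcome has about 71% power at 0.025 for the original differences. No further participants are needed if the sponsor accepts that.

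Naming a single primary gambling outcome at 6 months would hold the rate at 5% without a larger detectable difference. It would demote an outcome that the design deliberately named and powered, so it is an alternative for the sponsor to choose and not a requirement.
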